## Abstract

**Background:**

HealthyHearts NYC (HHNYC) will evaluate the effectiveness of practice facilitation as a quality improvement strategy for implementing the Million Hearts’ ABCS treatment guidelines for reducing cardiovascular disease (CVD) among high-risk patients who receive care in primary care practices in New York City. ABCS refers to (A) aspirin in high-risk individuals; (B) blood pressure control; (C) cholesterol management; and (S) smoking cessation. The long-term goal is to create a robust infrastructure for implementing and disseminating evidence-based practice guidelines (EBPG) in primary care practices.

**Methods/design:**

We are using a stepped-wedge cluster randomized controlled trial design to evaluate the implementation process and the impact of practice facilitation (PF) versus usual care on ABCS outcomes in 250 small primary care practices. Randomization is at the practice site level, all of which begin as part of the control condition. The intervention consists of one year of PF that includes a combination of one-on-one onsite visits and shared learning across practice sites. PFs will focus on helping sites implement evidence-based components of patient-centered medical home (PCMH) and the chronic care model (CCM), which include decision support, provider feedback, self-management tools and resources, and linkages to community-based services.

**Discussion:**

We hypothesize that practice facilitation will result in superior clinical outcomes compared to usual care; that the effects of practice facilitation will be mediated by greater adoption of system changes in accord with PCMH and CCM; and that there will be increased adaptive reserve and change capacity.

**Trial registration:**

NCT02646488

## Background

In 2011, the US Department of Health and Human Services launched the Million Hearts Campaign with an explicit goal of preventing one million heart attacks and strokes by 2017 [1]. A core component of the campaign is to improve implementation and systematic delivery of ABCS treatment guidelines: (A) aspirin in high-risk individuals; (B) blood pressure control; (C) cholesterol management through guideline-recommended use of lipid lowering medications (i.e., statins); and (S) smoking cessation. In order to accelerate adoption of Million Hearts guidelines in primary care practices as well as build capacity for their ongoing implementation and dissemination, the Agency for Healthcare Research and Quality (AHRQ) launched EvidenceNOW—a national initiative that aims to transform health care delivery in small primary care practices by building critical infrastructure to integrate the most up-to-date research into practice to improve the heart health of their patients [2].

There is a strong rationale for targeting small practices (i.e., fewer than 10 providers). First, small practices continue to provide primary care for a significant proportion of the population. More than half of primary care office visits occur in small practice settings [3–5]. Second, small practices face daunting challenges in redesigning their system and care processes to meet regulatory requirements for practice transformation. Most small practices lack the resources and staff expertise related to information systems, goal setting, data analysis, and practice redesign to coordinate a complex set of multilevel system changes without external assistance [6]. One implementation strategy that may effectively overcome these barriers is practice facilitation (PF) [7, 8].

PF provides external expertise to help organizations make meaningful practice changes that are tailored to local context and in accord with current practice transformation models like the chronic care model (CCM) and patient-centered medical home (PCMH) [9, 10]. Implementation science literature suggests that PF’s emphasis on building organization capacity to adapt clinical evidence to the specific circumstances of the practice environment may be more effective in achieving sustainable improvements in guideline-concordant care and patient outcomes in primary care settings compared to single component (e.g., audit and feedback alone) and other multicomponent guideline implementation strategies (e.g., learning collaborative) [7, 8, 11–22]. A recent systematic review of PF interventions demonstrated that primary care practices with the support of a facilitator are almost three times more likely to implement evidence-based guidelines compared with usual care practices [7]. Despite this evidence, the effectiveness of PF remains largely untested in small primary care practices, especially those that serve vulnerable and underserved minority populations.

HealthyHearts NYC (HHNYC), one of seven cooperatives funded through the EvidenceNOW initiative, is a stepped-wedge cluster randomized controlled trial designed to evaluate the impact of PF compared to usual practice on implementation of the Million Hearts ABCS treatment guidelines in 250 small primary care practices, where a significant proportion of vulnerable populations in NYC receive care.

The specific aims of the HealthyHearts NYC project are to (1) compare the effect of PF versus usual care on ABCS outcome measures; (2) identify baseline organizational characteristics (e.g., site level adaptive reserve, organizational change capacity) that are associated with intervention outcomes; (3) use qualitative methods to assess barriers and facilitators to implementing practice change and achieving ABCS outcomes among high- and low-performing practices in the study; and (4) evaluate the intervention-specific costs per patient and per site.

## Methods

### Study setting

HHNYC is a partnership between New York University School of Medicine (NYUSOM) and the NYC Department of Health and Mental Hygiene (NYCDOHMH) Primary Care Information Project (PCIP), which has over 1300 small- to medium-sized primary care practices in its regional extension center [23]. The study is being conducted in small practices in NYC that are part of PCIP’s practice network. NYC has the largest (8.5 million) and most diverse population of any city in the US (26 % Hispanic, 26 % black, and 13 % Asian) [24]. Although NYC has achieved substantial decline in CVD-related deaths, heart disease still remains the number one cause of death and significant disparities by income and race/ethnicity persist. Residents of NYC’s poorest neighborhoods, where many of the study small practice sites are located, consistently have higher mortality rates from almost all diseases, including CVD, compared with residents in its wealthiest neighborhoods [25, 26]. For example, hypertension-related death rates among black New Yorkers are four times higher than among white New Yorkers (35 vs. 9 per 100,000 adults). Additionally, patients in PCIP network practices with a greater proportion of low income and minority patients in their panels are less likely to achieve target measures for blood pressure control and smoking cessation measures [27].

### Study design

HHNYC is a stepped-wedge cluster randomized controlled trial that is designed to evaluate the implementation process and the impact of PF (intervention) compared to usual practice (control), on implementation of the Million Hearts ABCS treatment guidelines in 250 primary care practices. All practice sites begin as part of the control condition and are block-randomized into four waves with each wave beginning 3 months after the start of the prior wave and lasting for 12 months (see Table 1). All clusters eventually receive the intervention, and outcomes will be measured every 3 months in all clusters. We anticipate, conservatively, a 15 % attrition rate; therefore, we have enrolled 290 sites to ensure that enrollment of the required 250 sites is achieved at the end of the study. This study has received Institutional Review Board approval by the New York University School of Medicine.

**Table 1 Tab1:** Stepped-wedge study design

	Year 1 (months)				Year 2 (months)				Year 3 (months)			
Clusters	3	6	9	12	15	18	21	24	27	30	33	36
	Time period											
1 (80 sites)		C	X	X	X	X	F	F				
2 (70 sites)		C	C	X	X	X	X	F	F			
3 (70 sites)		C	C	C	X	X	X	X	F	F		
4 (70 sites)		C	C	C	C	X	X	X	X	F	F	

*C* control period, *X* intervention period, *F* follow up period

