### Analysis plan

#### Aim 1

The primary outcomes are the proportion of patients who reach clinical goals based on national guidelines for (a) aspirin use, (b) HTN control, (c) blood cholesterol management, and (d) smoking cessation assistance at the end of the intervention (12 months) period and 6 months post-intervention. Each of the four hypotheses referring to the four primary outcomes will be tested separately with a two-sided test with *α* = 0.05, i.e., no adjustment for multiple testing will be applied. The analysis of effect of PF on the ABCS outcome measures in the context of a stepped-wedge design will be based on a generalized linear mixed model (GLMM). In particular, to assess the intervention effect, we will use a Poisson model with random site and provider within site effects. Each model will be as follows:1$$ \log \left({C}_{it}\right)=\mu +{\beta}_1t+{\beta}_2{I}_{it}^{PF}+{\beta}_3{I}_{it}^{PF}\left(t-{s}_i\right)+\gamma {Z}_i+{b}_i+ \log \left({E}_{it}\right), $$

where *C*
_*it*_ is the number of patients in site *i* who (a) had received aspirin, (b) had controlled blood pressure, (c) had controlled cholesterol, or (d) received smoking cessation counseling during period *t*, for *t* ∈ (0, 1, …, 11). Each period is 3 months, and *t* = 0 is the baseline quarter. *I*
_*it*_^PF^ is an indicator variable, and *I*
_*it*_^PF^ = 1 if site *i* has been assigned to the PF intervention at period *t*, *I*
_*it*_^PF^ = 0 otherwise. *s* is the time period when the PF intervention begins for site *i. Z* is a site-level indicator variable, *Z* = 1 if site *i* has three or more providers, *Z* = 0 otherwise. *E*
_*it*_ is the number of patients at site *i* who were eligible to be counted during period *t*. The eligible pool of patients *E*
_*it*_ will be different for each outcome and has been described in detail in Table 1. Log(*E*
_*it*_), considered the “offset” in the Poisson regression model, is a random effect for site *i* with mean 0 and variance *σ*
_*b*_^2^. The estimation via model (1) takes into account a general time trend and allows for the intervention effects to grow over time following implementation of the intervention.

Our primary outcome of interest for each of the four models is proportion of patients who meet clinical goals (described above) at 12 months. In each model, this effect (after taking into account general time trends) would be captured by *β*
_2_ + 3*β*

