### Power/effect size analysis

With the pre-specified sample size of 250 sites and design (wedge design with four strata/waves starting 3 months apart), we investigated the intervention effects under each of the primary hypotheses in Aim 1, that are detectable with at least 80 % power of a two-sided significance test with *α* = 0.05 (Appendix). Conversely, we assessed the power to detect effects that are clinically meaningful and realistic. For each of the four outcomes, we are interested in the proportion of eligible patients in a site who meet guideline recommendations for ABCS clinical care in the fourth quarter of the PF intervention (i.e., month 12 of the intervention) relative to compliance proportions at baseline.

Using conservative (i.e., low) eligibility levels of an average of 50 patients per physician per quarter, we will have over 80 % power to detect a 2.0 % change, assuming a starting compliance rate of 20 % (increasing from 20.0 to 22.0 %). Finally, we have little information to estimate the current levels of variation between sites (*σ*
_*b*_^2^). However, the simulations suggest that power does not decrease when the assumed variance is increased from 0.10 to 0.25 on the log scale. If in fact the variance is lower, closer to 0.01 or 0.05, power is increased substantially to over 95 %.

#### Aim 2

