_3_). For each of the 1000 data sets, we estimated the same model and tested the hypothesis that *β*
_2_ + 2*β*
_3_ (the effect size in the third quarter) was significantly different from 0. The proportion of significant results represented the power of the study under the specific set of assumptions.

For the purposes of simulation, we assumed 63 sites in each stratum, for a total of 252 sites. Preliminary simulations indicated that larger general time trends (*β*
_1_) and larger number of patients in a physician panel both increased power. Based on this, our final simulations included very conservative assumptions of zero growth trend (*β*
_1_ = 0) and average eligibility size (*E*
_*jt*_) of 50 patients per physician at the practice. In the simulation, a general level of *E*
_*j*_ for site *j* was generated from a Poisson distribution of mean 50 × the number of physicians at the site. The value of *E*
_*jt*_ for a particular time period was calculated (and rounded to the nearest integer) as *E*
_*ij*_ + *e*
_*ijt*_, where *e*
_*ijt*_ ~ *N*(mean = 0, sd = 2). For each site *j* during period *t*, log(*C*
_*jt*_) was generated using equation (2). A value *C*
_*jt*_, the number of patients in compliance for site *j* during period *t* was generated from a Poisson distribution with mean *C*
_*jt*_.

Table 4 shows results after varying effect size parameters (*β*
_2_ & *β*
_3_), baseline compliance rate (*π*
_0_), site-level random effect variance (*σ*
_*d*_^2^), and patient eligibility levels (*E*). The current baseline compliance rates for the four measures are 49 % (blood pressure control), 33 % (LDL control for cholesterol), 35 %, (aspirin recommendation), and 20 % (smoking cessation referral). The number of patients that will be eligible in each 3-month period is based on an average physician roster of approximately 1,000 patients. Currently, 30 % of those patients have hypertension, 30 % have hyperlipidemia, and 20 % smoke. If we make a conservative estimate that 25 % of the patients will have an office visit per 3-month period, each eligible category will range from 50 to 75 patients. In Table 4, we use the lowest (most conservative) assumption of 50 patients, which reflects the likely size of the smoking group. At this level of eligible patients, we will have over 80 % power to detect a 2.2 % change, assuming a starting compliance rate of 20 % (increasing from 20.0 to 22.2 %) and between-site variance of 0.10 on the log scale.

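### At the stated 15 % attrition, 290 enrolled sites leave about 246, not the 250 the plan says they ensure; the effect on power is about 1 point or less

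*Protocol article*

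**What the plan says.** The Study design section of the protocol article gives the attrition assumption, "We anticipate, conservatively, a 15 % attrition rate", and draws the enrolment figure from it: "we have enrolled 290 sites to ensure that enrollment of the required 250 sites is achieved at the end of the study". Table 1 in that section allocates 80, 70, 70 and 70 sites to the four waves, which adds up to 290.

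The Power/effect size analysis section treats 250 as the design size: "With the pre-specified sample size of 250 sites and design". The Appendix explains the number actually simulated: "For the purposes of simulation, we assumed 63 sites in each stratum, for a total of 252 sites". Its headline result for the least favourable outcome is "we will have over 80 % power to detect a 2.2 % change, assuming a starting compliance rate of 20" %, with a between-site variance of 0.10 on the log scale.

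**The concern.** The enrolment figure is presented as following from the 15 % rate and as guaranteeing 250 sites at the end. A reader can check this in one line, and it fails. At the plan's own rate, 43.5 of the 290 sites are lost, while the gap between 290 and 250 leaves room to lose only 40.

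What is at stake is limited. The 250 is the stated sample size on which the power claim rests, and the claim for the least favourable case is only that power exceeds 80 %, with no margin given. If the true margin is very thin, a few lost sites could take it just below 80 %.

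**Working it through.** **Inputs**

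- Attrition d = 15 %, enrolled 290, required 250 (Study design).
- Simulated sites 4 × 63 = 252 (Appendix).
- Two-sided α = 0.05 for each outcome (Analysis plan, Aim 1), so the critical value is 1.960.
- Power over 80 % for 20.0 % to 22.2 % (Appendix).

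**Step 1: can 290 be reproduced?**

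- Standard inflation N/(1 − d): 250/0.85 = 294.1, so 295. From 252: 252/0.85 = 296.5, so 297. Neither gives 290.
- Shortcut N × (1 + d): 250 × 1.15 = 287.5, so 288. From 252: 252 × 1.15 = 289.8, so 290.

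The figure therefore matches the multiplication shortcut applied to 252, or 287.5 rounded up. The article does not say how 290 was obtained, so its origin is an inference.

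**Step 2: what does 290 deliver?**

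- Expected sites at the end: 290 × (1 − 0.15) = 246.5.
- Against 250: 3.5 short (3.5/250 = 1.4 %). Against 252: 5.5 short (5.5/252 = 2.2 %).
- Largest attrition that keeps 250: (290 − 250)/290 = 13.8 %. To keep 252: 38/290 = 13.1 %.

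**Step 3: how likely is 250 at the plan's own rate?** Assume, as the article does not, that each site is lost independently with probability 0.15. The number retained is then Binomial(290, 0.85), and P(at least 250 retained) = 0.316, about 32 %.

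**Step 4: effect on power.** With everything else fixed, the standardised effect scales with the square root of the number of sites:

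power(n) = Φ[(1.960 + z_p) × √(n/252) − 1.960],

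where p is the power at 252 sites, z_p is its normal quantile, √(246.5/252) = 0.9890 and √(250/252) = 0.9960. For p = 80 %, z_p = 0.842 and 2.802 × 0.9890 − 1.960 = 0.811, which gives 79.1 %.

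| Power at 252 (assumed) | At 250 | At 246.5 |
|---|---|---|
| 80 % | 79.7 % | 79.1 % |
| 81 % | 80.7 % | 80.1 % |
| 82 % | 81.7 % | 81.2 % |
| 85 % | 84.7 % | 84.2 % |
| 90 % | 89.8 % | 89.4 % |

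The loss at 246.5 sites is at most 0.9 points in this table. Solving for the power at 252 that leaves exactly 80 % at 246.5: z_p = 2.802/0.9890 − 1.960 = 0.873, so p = 80.9 %. The claim survives complete loss of the missing sites if the simulated power was about 81 % or more.

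**Step 5: cross-check with the stepped-wedge layout.** An approximate generalised least squares calculation used the log-linear model with a random site intercept. It took Table 1's control and intervention quarters, a 20 % baseline, a ratio of 1.11 and a site variance of 0.10. It assumed 50, 70, 100 or 150 eligible patients per site and quarter. Going from 252 to 246.5 sites in equal waves lost between 0.5 and 1.0 points, which agrees with step 4. Spreading the 246.5 sites in the 80:70:70:70 proportions of Table 1 instead of equally lost a further 0.1 to 0.4 points. Absolute power in these runs ranged widely with the assumed number of eligible patients per site. The article gives 50 per physician but not the number of physicians per site, so only the differences are usable.

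**The case against.** The strongest reply is that this is rounding. The 290 is 5 sites, or 1.7 %, below 295. The plan calls its 15 % conservative, and 13.8 % would suffice. If 15 % is read as a share of the required 250 rather than of the sites enrolled, the 40 spare sites (40/250 = 16 %) cover it. In addition, outcomes are measured every quarter in all clusters and modelled with a site random effect, so a site that leaves partway could still contribute its earlier quarters. On that view 246.5 complete sites is a pessimistic basis for power, although the article does not say how such data are handled.

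Most of this stands as an argument about size. It does not rescue the sentence. An attrition rate is ordinarily a share of those enrolled, and wording that promises to ensure a required number asks more than approximate agreement.

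Three stronger readings are tempting, and the document supports none of them.

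- A reader might infer that 290, 250 and 252 are three conflicting sample sizes. They are different quantities: sites enrolled, sites required at the end, and sites used in the simulation. The Appendix states openly that 252 is four strata of 63. Since 250 does not divide by four, this is the nearest equal split that reaches it.
- A reader might infer that the power claim fails, or that the shortfall uses up most of its margin. The article says only that power is over 80 % and gives no margin. Any absolute figure needs an assumed number of compliant patients per site and quarter that the article does not supply.
- A reader might infer that simulating equal waves while randomising 80/70/70/70 is a material error. The cross-check puts that effect at a few tenths of a point.

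The simulated case is also the least favourable one. The Appendix reports 92 % power with 70 eligible patients, and baselines of 33 % to 49 % for the other three outcomes, where power is higher.

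**Conclusion.** The point holds as a minor error in a stated sample size. With 15 % of 290 sites lost, about 246 remain, 1.4 % below the 250 said to be ensured. This part is exact and rests only on reading the 15 % as a share of enrolled sites. If sites are also lost independently, the plan would reach 250 about one time in three.

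The consequence for power is about 1 point or less from the number of sites. This assumes that lost sites contribute nothing and that information scales with site count. The claim of over 80 % power is not refuted. Whether it holds at 246 sites in the least favourable case depends on whether the simulated power was nearer 80 % or 81 %, which the article does not say. No design choice, analysis or conclusion of the trial is threatened.

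**What to change.** In the Study design section, either give the expected final number as about 246 sites at 15 % attrition, or say that 250 sites will remain if attrition is at most 13.8 %. In the power section or Appendix, confirm the claim of over 80 % power at about 246 sites by re-running the existing simulation code. Using the randomised 80/70/70/70 proportions in that run costs nothing more and matches Table 1. If the result falls slightly under 80 %, report it as it is.

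The cost is one sentence and one simulation run. Enrolment is complete, and no further sites are needed.

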### Study site eligibility

We recruited practices from PCIP’s practice network, which was established in 2005 to improve health outcomes in low-income communities in NYC. This network includes over 1300 small- to medium-sized practices with significant numbers of Medicaid or uninsured patients. To be eligible, practice sites were required to have <10 full-time equivalent (FTE) healthcare providers (physician, nurse practitioner, physician assistant); have implemented an electronic health record (EHR) for at least 1 year; sign an agreement with PCIP to participate in PCIP’s Hub Population Health System, an EHR query architecture; have no immediate future plans to participate in a CVD-related quality improvement initiative; have no plans to change EHRs in the next 18 months; be willing to identify a site coordinator to work with study staff on all aspects of the intervention; and be located in NYC [28]. We will recruit 40 of the sites that are enrolled in the study to participate in the qualitative assessment described below. For the qualitative interviews, sites will be chosen to ensure representation across different geographic locations in NYC and practice size.

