### Patient eligibility

Data is being abstracted for patients who: (a) have at least one of the ABCS risk factors (i.e., eligible for aspirin, has a diagnosis of hypertension, meets criteria for blood cholesterol management, and/or is a current smoker); (b) have received care at the site in the last 12 months; and (c) are age >18 years. Patients eligible for aspirin are those with a documented ICD (ICD-9/10) code for ischemic vascular disease in the last 12 months. Similarly, patients with a diagnosis of hypertension must have a documented ICD code for the targeted risk factor. Patients with hyperlipidemia based on an ICD code or who otherwise meet criteria for cholesterol management are identified by laboratory results for LDL cholesterol as well as ICD codes. Smokers are identified by documentation of current smoking status in the EHR (e.g., meaningful use measure) during the past 24 months.

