#### Outcome measures and data source

The primary outcome is the proportion of patients who reach clinical goals for hypertension, blood cholesterol management, aspirin use, and smoking cessation assistance (Table 2). The measures were defined by AHRQ EvidenceNOW and finalized through a collaborative process across all the seven funded groups. We will collect data for the 12-month period prior to implementing the intervention, during the 12-month intervention period, and then 6 months post-intervention. These data will be extracted from the EHRs of all 250 participating sites using PCIP’s Hub, a query architecture that enables execution of queries in independent EHRs of the participating practices with data subsequently transmitted to a secure centralized clinical data repository [28]. The Hub provides a platform for HHNYC to extract numerator and denominator data for the ABCS measures. The underlying data quality/integrity of practices connected to the Hub is based on assessment of documentation patterns at the practices (e.g., completeness of use of routine structured data fields such as demographics, diagnosis, vital signs, and smoking status) as well as utilization of electronic laboratory interfaces, to ensure laboratory results data are available in electronic format [36].

**Table 2 Tab2:** Outcome measures, data source, and data collection timeline

Domain	Measures	Data source	Administration

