Primary outcomes	• Aspirin: percent of patients aged 18 years and older with ischemic vascular disease (IVD) with documented use of aspirin or other antithrombotic. • Blood pressure management: 1) Percent of patients aged 18–85 who had a diagnosis of hypertension (HTN) and whose blood pressure (BP) was adequately controlled (<140/90). 2) Percent of patients aged 60–85 without diabetes (DM) or chronic kidney disease (CKD) with controlled BP (<150/90), 3) Percent aged 18–85 with DM or CKD with controlled BP (<140/90) • Cholesterol management: 1) Percentage of patients aged >21 diagnosed with ASCVD who are on statin therapy. 2) Percentage of patients aged >21 with history of LDL >190 mg/dL without ASCVD who are on statin therapy. 3) Percentage of patients aged 40–75 with diabetes without ASCVD and LDL 70–189 mg/dL who are on statin therapy • Smoking cessation support: Percentage of patients aged 18 years or older who were screened about tobacco use one or more times within 24 months and who received cessation counseling intervention if identified as a tobacco user.	EHR	Baseline, quarterly during intervention period, at the end of intervention (12 months), and 6 months post intervention
Secondary outcome: practice change capacity	• Organizational change process capacity • Adaptive reserve	Provider and staff survey	Baseline, at the end of intervention (12 months) and 6 months post intervention

The secondary outcome is changes in primary care practice capacity captured through the use of the change process capacity questionnaire and the 23-item adaptive reserve scale [31, 32]. These measures will be obtained through provider and staff surveys at three time points: baseline, immediately following the 12-month intervention and 6 months post-intervention.

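### Sites may enter with 12 months of EHR, but the smoking outcome looks back 24 months; any resulting drift is of unknown sign and is not fully removed by the model's linear time term

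*Protocol article*

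**What the plan says.** Under Study site eligibility, a practice must "have implemented an electronic health record (EHR) for at least 1 year".

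The smoking row of Table 2 counts adults "screened about tobacco use one or more times within 24 months and who received cessation counseling intervention if identified as a tobacco user". Patient eligibility uses the same window length: "Smokers are identified by documentation of current smoking status in the EHR (e.g., meaningful use measure) during the past 24 months". It also requires that patients "have received care at the site in the last 12 months".

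Sites are "block-randomized into four waves with each wave beginning 3 months after the start of the prior wave", and Table 1 gives waves 1 to 4 one, two, three and four control quarters. Under Outcome measures and data source the article adds: "We will collect data for the 12-month period prior to implementing the intervention".

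For model (1), the Analysis plan defines the smoking count as patients who "received smoking cessation counseling during period" t, each period being 3 months. Calendar time enters only as β1t, and the model is said to be one that "takes into account a general time trend and allows for the intervention effects to grow over time". The 12-month effect is β2 + 3β3.

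**The concern.** A site admitted at the minimum cannot fill a 24-month window in its first study quarters. The window lengthens each quarter and is complete once the EHR is 24 months old. All sites start in control, so the incomplete windows fall mostly before facilitation and the complete ones mostly after it.

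If truncation changes the recorded proportion, the smoking rate moves without any change in care and then stops moving. A straight line cannot follow that shape, so part of the artefact passes into the intervention terms. Nothing in the article restricts or adjusts the smoking analysis for length of EHR history. The outcome is tested on its own at two-sided 0.05 for a change of about two percentage points, so a modest artefact could be visible.

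**Working it through.** **Inputs.** From the article: 12-month minimum EHR history; 24-month look-back; Table 1 (80, 70, 70 and 70 sites; first control column at month 6; four intervention quarters per wave); 25% of patients seen per quarter (Appendix); target 20% to 22% (Power/effect size analysis). The article gives no figure for the look-back itself. The target on the model's scale is log(22/20) = 0.095. Assumed, because not given: the share q of sites at the minimum, and the chance that a visit produces a smoking entry.

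**Step 1: where truncation falls.** Take every site to have exactly 12 months of EHR at study month 0. Its history is then 18 months in the month-6 quarter, 21 at month 9 and 24 from month 12.

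- Control site-quarters: 80×1 + 70×2 + 70×3 + 70×4 = 710. Truncated: 290 (month 6) + 210 (month 9) = 500, or 70%.
- Intervention site-quarters: 290×4 = 1160. Truncated: 80 (wave 1, month 9), or 7%.
- Control share of all truncated site-quarters: 500/580 = 86%. If the 12 months are counted at month 3 it is 640/870 = 74%; at month 6, 710/1160 = 61%.

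**Step 2: direction.** Three readings are open.

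- Table 2: an adult whose only screening entry predates the EHR stays in the denominator and leaves the numerator. The recorded rate starts low and rises.
- Patient eligibility with the per-quarter count in the Analysis plan: truncation removes smokers from the denominator only. The rate starts high and falls.
- Numerator and denominator shrink together: the drift may cancel.

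**Step 3: illustrative size, Table 2 reading.** Let an entry arise only in a quarter with a visit. The recorded proportion relative to a full window is

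h(L) = [1 − 0.75^(L/3)] / [1 − 0.75^8],

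so h(18) = 0.822/0.900 = 0.913, h(21) = 0.963 and h(24) = 1. With a true effect of zero, I fitted log proportion by least squares weighted by number of sites, with an intercept for each wave and old/new EHR group, linear t, I and I(t − s), on the control and intervention quarters.

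| q | Bias in β2 + 3β3 | Share of 0.095 |
|---|---|---|
| 10% | −0.006 | 6% |
| 25% | −0.015 | 16% |
| 50% | −0.030 | 32% |

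Adding follow-up quarters coded as exposed gives −0.006, −0.014 and −0.029. If truncation hits the denominator instead, the 25% figure becomes +0.015.

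**Step 4: respecting the 12-month care requirement.** The formula in Step 3 keeps patients with no visit in the window, whom Patient eligibility excludes. Require at least one visit in the last four quarters and let a visit quarter yield an entry with probability p. The chance of an entry in n quarters is

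1 − {[(1 − 0.25p)^4 − 0.75^4] / [1 − 0.75^4]} × (1 − 0.25p)^(n−4).

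At q = 25% the bias is 0 for p = 1, −0.003 for p = 0.9, −0.016 for p = 0.5 and −0.028 for p = 0.2. The signs reverse under the denominator reading. Hence the range of nil to about 0.03 in absolute value.

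**Step 5: what removes it.** With period indicators in place of linear t, the bias in the Step 3 set-up is 0 at every q, given the same share of new sites in each wave. With linear t plus look-back months capped at 24, it falls to −0.0003, −0.0007 and −0.0014 for q = 10%, 25% and 50%.

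**The case against.** The strongest reply has four parts.

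**No site is shown to be affected.** The article does not say that any practice had under 24 months of EHR. If every analysed quarter has a full window, the bias is nil. This stands, and it is why the size can only be illustrated.

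**The direction is not settled.** A reader might infer that the newest sites' recorded rate must rise, or that this favours facilitation. The documents support neither. Smokers are identified over the same 24 months, and the modelled count is of counselling within a 3-month period, so the rate may fall or stay level. Where it does rise, a raw before-and-after comparison favours facilitation, but model (1) over-corrects and the error runs against it. A small error in favour appears under that reading if follow-up quarters are coded unexposed.

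**Larger effects are not supported.** A reader might take the 12 months of pre-intervention data to enter the model for every wave, which would enlarge the problem. But the Analysis plan starts at a single baseline quarter, t = 0, and Table 1 gives wave 1 one control quarter; the sentence on 12 months describes data collection. A reader might also extend the argument to the history of high LDL in Table 2. That defines a denominator, and its growth does not imply a rising statin proportion.

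**Randomisation and unseen documents.** EHR age precedes randomisation, so the drift is shared across waves in expectation. That is correct, but it protects the contrast only if calendar time is modelled flexibly enough. The measures come from the funder's initiative, and a fuller specification or analysis plan may hold look-back rules. Even so, the shorter site criterion, the 24-month windows and the linear term are all fixed in this article. The article's check on documentation completeness, which names smoking status, does not concern length of record.

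**Conclusion.** The point holds in a limited form. The site criterion is shorter than the smoking look-back, truncation at any affected site falls mainly in control quarters (61% to 86% of truncated site-quarters, depending on when the 12 months are counted), and a single linear time term does not fully absorb a drift that ends at 24 months.

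The sign of the resulting bias depends on a numerator and denominator choice that the article leaves open. Its size depends on the share of new sites and on recording habits, neither of which is given. At an assumed 25% of sites at the minimum it runs from nil to about 0.03 in absolute value, at most roughly 30% of the 0.095 target (0.028/0.095). This is a minor issue, confined to the smoking outcome.

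**What to change.** For the smoking outcome, do one of the following in model (1):

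- replace β1t with period indicators; or
- keep β1t and add a site-quarter covariate for months of available look-back, capped at 24.

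In either case, add a sensitivity analysis limited to site-quarters with 24 months of EHR history. Reporting EHR age at the baseline quarter would show whether the problem exists at all.

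**Cost.** The control and intervention quarters in Table 1 span eight periods, so period indicators mean seven parameters in place of one slope, with some loss of precision. The covariate adds one parameter. The covariate and the sensitivity analysis need each site's EHR go-live date; the eligibility check may have recorded only that one year had passed, so the date may have to be obtained.

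Exclusion should not be the primary rule. For sites with 12 months at study month 0, the quarters at months 6 and 9 would go, and these are all the control quarters of the newest wave 1 and wave 2 sites. Recruitment and the site criterion need not be reopened.
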